**Outcomes:**

The primary outcomes include the reoccurrence of MB events or CRNMB for patients who did or did not continue OACs, the composite of stroke and other thromboembolic events, bleeding or cardiovascular related mortality, and all-cause mortality. Secondary outcome is the prescription of any OACs after the occurrence of the major bleeding events (VKAs or NOACs). We also aim to explore the timing of reinitiating OACs from the indexed bleeding event until the date of OACs prescription, and whether patients have continued on the same OAC before the index haemorrhage event, were switched to another agent after bleeding have occurred (i.e. from warfarin to any NOACs or from any NOACs to warfarin) or received lone antiplatelet therapy.

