### Specific aims:

1. To determine the incidence of NVAF diagnosis in England from the year 2009 to 2019.
2. To determine the proportions of patients with NVAF and those with NVAF and cancer who were prescribed OACs, antiplatelet alone or no treatment.
3. To examine the temporal trends of prescribing different types of OACs (i.e. VKAs and NOACs), and assess the factors associated with not prescribing OACs including patient demographics, socioeconomic status, history of cancer and other comorbidities, stroke and bleeding risk.
4. To assess the effect of OACs prescribing vs. no OACs on the clinical outcomes (stroke, bleeding, and death) in a comparative cohort of NVAF patients eligible for anticoagulation after controlling for patients' comorbid conditions, frailty, age, and antiplatelets use.
5. To assess the rate of clinical outcomes (i.e. bleeding recurrence, stroke, and mortality) after MB events and how they relate to OACs resumption and the timing of restarting OACs after the MB event.
6. To explore the variability across patient groups regarding OACs resumption after MB events and whether patients have continued on the same OAC before the MB event, switched to another OACs or received lone antiplatelet therapy.
7. To assess and compare patients' risk for stroke and bleeding recurrence using HAS-BLED, CHA2DS2-VASC, HEMORR?HAGES and GARFIELD-AF risk assessment scores, at the time of the indexed major bleeding event.

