### **Definition of the study population**

Patients will be identified from CPRD, both GOLD and Aurum databases will be used as the primary care data source

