2. Phase 2 – Comparative study: For comparison of demographic variables and comorbidities among OACs treated and not treated individuals, independent sample t tests will be used for numeric variables, while Chi squared  $\chi^2$  tests or Fisher exact tests will be used for categorical variables. To control for imbalances in patient characteristics between cohorts, we will calculate an exposure-specific propensity score as the predicted probability of receiving OACs conditional upon individuals baseline covariate (as described in section M) using logistic regression models. Then we will consider applying propensity score matching methods to match each OACs unexposed controls to up to 5 NVAF OACs exposed cases using a calliper of 0.2 standard deviation (SD) of the propensity score logit. After matching, Cox regression will be used to compute hazard ratios (HRs) of the outcomes of interest, comparing exposure to OACs versus no OACs. Initially crude HRs will be obtained, then stratified by type of OACs (i.e., VKAs and NOACs) and adjusted for age, and other important covariates described in section N. In this phase immortal time bias would occur due to the definition of exposure, where in the time from AF diagnosis till receipt of OACs those in the “OACs prescribed group” cannot have the outcome by design, otherwise they would have been classified as non OAC users. To avoid the problem of immortal time bias, we will consider using time-varying exposures, where in a survival analysis, the time period previous to the index date of OACs initiation is reclassified as nonuser for those in the “OACs prescribed group”.

3. Phase 3 – Major bleeding events cohort: At first, we will use descriptive statistics to present the overall characteristics of this cohort who have experienced major bleeding events while taking OACs. After that patients will be divided to 2 groups one for the patients who resumed anticoagulation after the index major bleeding event and the other for the group who remained OACs free and will compare the patient characteristics between the two groups using Chi squared  $\chi^2$  tests, Fisher's exact tests, and analysis of variance, as appropriate. Survival (time-to-event) models will be constructed to compare the time between the indexed major bleeding to the earliest event of stroke, bleeding, or all-cause mortality considering if patients were restarted on OACs or not. In Cox models we will control for age, time to OACs resumption, CHA2DS2-VASc

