### **Plan for addressing confounding**

In phase 2, we aim to conduct a comparison between NVAF patients who were exposed to OACs (cases) and patients who were not exposed to OACs (controls). We will calculate an exposure-specific propensity score as the predicted probability of receiving OACs conditional upon the effect of potential confounders (described in section M). Then we will use a propensity score matching method to achieve similarity of measured confounders across cases and control groups. When estimating HRs using Cox regression models for the outcomes of interest among patient groups, we will also adjust for age, sex, IMD, stroke risk, bleeding risk, frailty, Charlson comorbidity index, and prescription of antiplatelets.

In phase 3, when looking at the predictors of restarting OACs after the indexed bleeding events we will take in account many confounders that could influence this decision, this will be done by using a multinomial logistic regression to adjust for the covariates described in section N. These covariates will also be considered when conducting survival analysis to compare the time between the indexed major bleeding to the earliest event of stroke, bleeding, or death among patients who restarted OACs and those who did not. Also, when evaluating the outcomes of restarting OACs we will consider the timing of restarting anticoagulation after bleeding, and stratify patients based on different time periods of OACs reinitiating.

In both phase 2 and 3, an additional analysis will be considered to assess the robustness of results to unmeasured confounding using the E-value methodology. This estimates what the relative risk would have to be for any unmeasured confounder to overcome the observed association of OACs prescribing with the clinical outcomes of stroke, bleeding, or mortality.

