## Limitations of study design

Data on patient characteristics and other covariates included in this study may not be fully complete in CPRD. One of the foremost limitations of this analysis was that we will not be able to calculate a full HAS-BLED and HEMORR2HAGES scores for each patient, and therefore fully ascertain bleeding risk, (as a high risk of bleeding may have led to an anticoagulant not being prescribed). Imputation methods will be explored and applied to minimize the impact of the missing data. Sensitivity analysis will also be carried to investigate the effect of the missing data on the results of the analysis, these includes alcohol consumption and labile INR for the calculation of HAS-BLED, and genetic factors included in the HEMORR2HAGES score. Due to the retrospective nature of the study, data on adherence to OACs may not be well recorded and difficult to assess. Also, we might not be able to capture the exact timing of reinitiating OACs after MB events, since some patients might resume anticoagulation in hospital settings and such information will not be available through HES APC linkage.

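### Phase 3 dates OAC restart by a prescription that in-hospital restarts cannot supply, so for admitted bleeds early restarts are recorded late, and the disclosed limitation has no analysis attached

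*Protocol*

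**What the plan says.** All references are to the Protocol.

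- **Definition.** Under Exposures, outcomes and covariates, Phase 3 Outcomes, the plan will "explore the timing of reinitiating OACs from the indexed bleeding event until the date of OACs prescription".
- **Aim.** Specific aim 5 relates outcomes after the major bleed to restarting: "how they relate to OACs resumption and the timing of restarting OACs after the MB event".
- **Models.** Data/statistical analysis, item 3, will "compare the time between the indexed major bleeding to the earliest event of stroke, bleeding, or all-cause mortality", so follow-up also starts at the bleed. The restart interval enters the models: "In Cox models we will control for age, time to OACs resumption, CHA2DS2-VASc".
- **Strata.** Plan for addressing confounding will "stratify patients based on different time periods of OACs reinitiating". No cut-points are given.
- **Data.** Under Definition of the study population, "both GOLD and Aurum databases will be used as the primary care data source". The linked patient-level sources are HES APC and ONS deaths. Hospitalised bleeds come from HES.
- **Limitation.** Limitations of study design says "we might not be able to capture the exact timing of reinitiating OACs after MB events", because "some patients might resume anticoagulation in hospital settings and such information will not be available through HES APC linkage".

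**The concern.** The protocol does not call the date in the definition a primary care date. It becomes one in effect, because no other listed source holds prescriptions. A patient who restarts on the ward is given the date of a later primary care prescription, which will normally follow discharge. A patient whose stay exceeds the upper limit of the earliest stratum therefore cannot normally enter that stratum, whatever the true restart date.

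The Study background cites restart times after intracranial haemorrhage of 72 hours to 30 weeks. The early end of that range is the part most exposed to this error. If longer stays go with worse prognosis, the early stratum will look healthier than it should, and part of any apparent effect of timing could come from how restart was dated.

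**Working it through.** **1. The passages side by side.** The definition runs from bleed to prescription. The limitations section says in-hospital restarts are not available. The Cox models and the strata use the interval without modification. The planned sensitivity analyses concern missing covariates and incomplete HAS-BLED and HEMORR2HAGES items. The E-value concerns unmeasured confounding. Time-varying exposure is described only for Phase 2. Nothing addresses a misdated restart. The plan states no figure on this point, so there is none to reproduce.

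**2. Direction of the error.** Let T be the true restart day after the bleed, L the length of stay, and G the lag from discharge to the first primary care prescription. The recorded day is

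R = T if T ≥ L; R = L + G if T < L.

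For an in-hospital restart the error is R − T = (L − T) + G, which is always positive. Invented example: T = 5, L = 20, G = 10 gives R = 30, which is 25 days late.

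**3. How many early restarts are misdated.** Every input here is an assumption:

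- T log-normal, median 14, 30 or 60 days, log-SD 1.0, limited to 3–210 days (the cited 72 hours to 30 weeks);
- L log-normal, log-SD 0.8, independent of T;
- G uniform from 0 to an upper limit of 0, 14 or 28 days;
- an illustrative early stratum of 14 days or less;
- 200,000 simulated patients per scenario.

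| Median stay | Restarted in hospital | True restarts ≤14 days recorded later | Rank correlation of R with L, all resumers |
|---|---|---|---|
| 5 days | 3–20% | 10–32% | 0.01–0.34 |
| 10 days | 8–40% | 34–61% | 0.05–0.53 |
| 20 days | 20–61% | 67–85% | 0.17–0.73 |

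Misdating appears in every scenario. Among in-hospital restarters alone, the correlation of R with L is 0.61 to 1.00.

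**4. What this does to the strata.** Assume further that 30% of bleeds are severe, with median stay 18 days against 6 (log-SD 0.6) and death hazards of 0.30 against 0.12 per year. True restart is unrelated to severity and has no effect on death. One-year death is 1 − exp(−0.30) = 25.9% in severe and 1 − exp(−0.12) = 11.3% in other patients, so 0.30 × 25.9 + 0.70 × 11.3 = 15.7% overall. Across the nine combinations of restart median and lag:

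- 25–52% of true restarts within 14 days are recorded later;
- the early stratum holds 8–14% severe patients instead of 30%;
- one-year death is 12.6–13.5% in the early stratum and 15.4–18.8% in the later ones (15–42 and over 42 days).

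Hand check: with 8% and 14% severe, the expected early-stratum death is 0.08 × 25.9 + 0.92 × 11.3 = 12.5% and 0.14 × 25.9 + 0.86 × 11.3 = 13.3%. This agrees within simulation error. The gradient is spurious by construction. It appears even where only 6% restart in hospital.

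**5. Does a discharge clock cure it?** Keep the severity mix, draw T uniform from 3 to 95 days independent of severity, and record in-hospital restarts at discharge. One-year death in the three strata is then 13.5/16.1/15.9% on the bleed clock and 17.6/15.7/14.8% on the discharge clock. The discharge clock reverses the gradient. If instead the delay after discharge is unrelated to severity, the discharge clock is flat (15.7/15.9/15.7%) and the bleed clock is not (12.6/14.9/16.5%). Which clock is less biased depends on facts the document does not give.

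**The case against.** The strongest reply is that the authors saw the problem and said so, in conditional terms, and that cut-points and sensitivity analyses are commonly left to a statistical analysis plan that is not shown. This is fair as far as it goes: it is a disclosed bias, not an unnoticed contradiction. But the protocol itself fixes the time origin, the end point, the Cox covariate and the use of strata. For incomplete risk scores the same limitations section names imputation and a sensitivity analysis; for restart dates it names nothing.

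A second reply is that the simulated gradient is confounding by severity and vanishes within severity level. The models adjust for age, CHA2DS2-VASc, HAS-BLED, Charlson index and frailty, and bleed site is a listed covariate. This stands in part. How well those variables capture the severity of the bleed is unknown, and adjustment does not correct a wrong date.

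A third is that the Phase 1 rule counting INR records as VKA exposure would reduce misdating. The Phase 3 definition does not carry it over.

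Three stronger readings should be resisted:

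- **That the timing strata simply sort patients by length of stay.** This holds for in-hospital restarters. Across all resumers the correlation can be as low as 0.01, and bleeds without admission are untouched. The protocol gives no share of bleeds that are admitted.
- **That re-bleeds between the true and recorded restart count as off-OAC.** For Phase 3 the protocol describes a resumed group and an OAC-free group, not time-varying exposure. A patient who restarts on the ward, re-bleeds and later has a primary care prescription falls in the resumed group.
- **That the clock should simply move to discharge.** Step 5 shows that this can create the opposite bias. It also changes the question in Aim 5, which is timed from the bleed.

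**Conclusion.** The point stands in a limited form. For admitted bleeds, restarts made in hospital can only be dated late, so the early strata are depleted of longer-stay patients and the later strata contaminated. The direction follows from the definition and the stated data sources. The size does not: 10% to 85% of true restarts within 14 days misdated, and a spurious one-year mortality difference of about 2 to 6 percentage points (15.4 − 13.5 = 1.9; 18.8 − 12.6 = 6.2), rest on assumed stays, lags, severity mix and cut-points. The mortality figures are also unadjusted and ignore deaths before restart. The consequence is for the timing part of Aim 5, and above all for conclusions about very early restart. A change is worth making because the limitation is acknowledged but not handled, and the necessary dates come with data already requested.

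**What to change.** Keep the bleed-based interval as the main definition, and state that its end point is the first primary care OAC prescription. Add to Data/statistical analysis, item 3, and to Plan for addressing confounding, using HES APC admission and discharge dates:

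1. A sensitivity analysis for admitted bleeds that starts follow-up and the restart clock at discharge, with in-hospital re-bleeds and deaths reported separately.
2. A sensitivity analysis for patients whose first primary care prescription falls within a fixed, pre-stated window after discharge, varying the restart date between admission (or discharge) and that prescription.
3. Length of stay reported by timing stratum and adjusted for in the timing models. Show results with and without this adjustment, since part of the stay may follow an in-hospital restart.

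Limit conclusions about very early restart to what these analyses agree on.

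The cost is a few derived dates and some extra model runs, with no new data request. In the discharge-based analysis, in-hospital events leave the restart comparison, where exposure is unknown anyway. Neither clock is unbiased, so the timing result should be presented as a range.

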**Covariates:**

- Patients' demographic information (age, gender, ethnicity, body mass index (BMI), geographic location (rural vs. urban), smoking status, alcohol consumption, Charlson comorbidity index for the severity of comorbidity (Appendix 3 and 4), electronic frailty index (eFI), and the index of multiple deprivation (IMD).
- Clinical covariates such as CHA2DS2-VASc, GARFIELD-AF, HAS-BLED, and HEMORR2HAGES risk assessment scores all at the time of the index haemorrhage event.

- Anatomic location of the index MB event will be identified and classified according to the critical site of bleeding (i.e., intraspinal, intracranial, intraocular, intra-articular, pericardial or other bleeding sites).

## **Data/statistical analysis**

1. Phase 1 - NVAF cohort: Annual and crude incidence rates of NVAF cases will be calculated and expressed as person-time at risk with 95% confidence intervals (95% CI). Incidence rates will be calculated by dividing the number of new diagnosed NVAF cases each year by the total population at risk during the same year. NVAF incidence in each calendar year of the study period (2009-2018) will be stratified by age and further standardized by age and deprivation quantiles. Status of anticoagulation therapy will be classified as either OAC prescribed or OAC not prescribed. OAC prescribed patients are those who received prescriptions for OACs during the study period. Treatment patterns for OAC users will be evaluated for OACs continuation, discontinuation or switched). OACs not prescribed will be defined as no prescription record of an OACs at any time after NVAF diagnosis, this will also include patients prescribed lone antiplatelet therapy. Proportions of patients prescribed antiplatelets will be described for both OACs prescribed and not prescribed patients. Baseline demographic, and clinical characteristics, and status of cancer diagnosis across OACs prescribed and not prescribed groups will be presented as number and percentage, mean $\pm$  (SD), or median (interquartile range), as appropriate. For both groups' eligibility for OACs will be described and categorized based on stroke risk according to CHA2DS2-VASc score. Trends in OACs initiation, switching from antiplatelet only to OACs, and from VKA to NOAC will be explored for each year and further stratified by eligibility for OACs and deprivation quantiles. To identify variables independently associated with OACs prescribing multivariate logistic regression models will be used and fitted with the covariates described in section N. Similarly, in a separate analysis for patients with NVAF and previously diagnosed cancer multivariate logistic regression models will be fitted to explore variables independently associated with OACs prescribing (i.e, cancer types and metastasis status). The level of statistical significance was set at  $P < 0.05$ .

2. Phase 2 – Comparative study: For comparison of demographic variables and comorbidities among OACs treated and not treated individuals, independent sample t tests will be used for numeric variables, while Chi squared  $\chi^2$  tests or Fisher exact tests will be used for categorical variables. To control for imbalances in patient characteristics between cohorts, we will calculate an exposure-specific propensity score as the predicted probability of receiving OACs conditional upon individuals baseline covariate (as described in section M) using logistic regression models. Then we will consider applying propensity score matching methods to match each OACs unexposed controls to up to 5 NVAF OACs exposed cases using a calliper of 0.2 standard deviation (SD) of the propensity score logit. After matching, Cox regression will be used to compute hazard ratios (HRs) of the outcomes of interest, comparing exposure to OACs versus no OACs. Initially crude HRs will be obtained, then stratified by type of OACs (i.e., VKAs and NOACs) and adjusted for age, and other important covariates described in section N. In this phase immortal time bias would occur due to the definition of exposure, where in the time from AF diagnosis till receipt of OACs those in the “OACs prescribed group” cannot have the outcome by design, otherwise they would have been classified as non OAC users. To avoid the problem of immortal time bias, we will consider using time-varying exposures, where in a survival analysis, the time period previous to the index date of OACs initiation is reclassified as nonuser for those in the “OACs prescribed group”.

3. Phase 3 – Major bleeding events cohort: At first, we will use descriptive statistics to present the overall characteristics of this cohort who have experienced major bleeding events while taking OACs. After that patients will be divided to 2 groups one for the patients who resumed anticoagulation after the index major bleeding event and the other for the group who remained OACs free and will compare the patient characteristics between the two groups using Chi squared  $\chi^2$  tests, Fisher's exact tests, and analysis of variance, as appropriate. Survival (time-to-event) models will be constructed to compare the time between the indexed major bleeding to the earliest event of stroke, bleeding, or all-cause mortality considering if patients were restarted on OACs or not. In Cox models we will control for age, time to OACs resumption, CHA2DS2-VASc

score and HAS-BLED score, Charlson comorbidity index, and eFI. In a secondary analysis, we will group patients who resumed OACs according to the type of anticoagulation drug used after the indexed bleeding events and compare the outcomes using Cox models in a similar manner. We will assess the proportional hazards assumption by examining Schoenfeld residuals and confirming that it is not violated. To identify variables independently associated with resuming

OACs after the indexed bleeding event multivariate logistic regression models will be used and fitted with the covariates described in section N. All the statistical analyses will be carried out using STATA (version 16).

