**Covariates:**

- Patients' demographic information (age, gender, ethnicity, body mass index (BMI), geographic location (rural vs. urban), smoking status, alcohol consumption, Charlson comorbidity index for the severity of comorbidity (Appendix 4), electronic frailty index (eFI), and the index of multiple deprivation (IMD).
- For the sub-group of patients with NVAf and history of cancer, cancer diagnosis will be assessed at the index date of NVAf diagnosis and classified by cancer type into breast, prostate, colorectal, haematological, lung, and other types, and by cancer metastasis status.
- Drugs that affect either stroke or bleeding, or commonly interact with OACs, such as antihypertensive drugs, statins, antiarrhythmics, antidiabetic drugs, anticonvulsants, non-steroidal

anti-inflammatory drugs, corticosteroids, systemic azoles, HIV protease inhibitors and ciclosporin. (Appendix 2).

- The CHA2DS2-VASc stroke risk score that consists of 9 points, one for each of: congestive heart failure (CHF), hypertension (HTN), age  $\geq 75$  years (x 2 points), diabetes mellitus (DM), prior stroke or transient ischemic attack (TIA) or thromboembolism (x 2 points), vascular disease, age 65 to 74 years, and sex category. Information included in the CHA2DS2-VASc score will be identified using Read codes (Appendix 3 and 4), except for age and sex, to build the score and assess the risk of stroke for all included patients in the cohort. Further categorization of eligibility for OACs will be carried according to individual CHA2DS2-VASc scores; “not eligible for OAC” if CHA2DS2-VASc score = 0 in males, or 1 in females; and “OAC eligible” if CHA2DS2-VASc score  $\geq 1$  in males, or  $\geq 2$  in females.

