  - Bleeding risk assessment using the HAS-BLED score which consists of 9 points, one for each of: hypertension, abnormal kidney or liver function (1 point each), stroke, history of bleeding or predisposition, labile INR, elderly ( $> 65$  years), and drugs/alcohol concomitantly (1 point each). All information included in the HAS-BLED score will be identified using Read codes (Appendix 3 and 4), except for age, to build the score and assess patients’ risk for bleeding. Labile INR will not be included since it is not recorded consistently in the CPRD and because we aim is to identify the presence of prescriptions for VKA rather than checking for patient’s adherence to VKA. Bleeding tendency or predisposition will be identified through Read codes for anaemia and gastric, duodenal, and peptic ulcers (Appendix 4). Also, since alcohol consumption is not well documented in primary care, whenever possible patients will score a point for this element if there is a Read code record of heavy or problematic drinking. The bleeding risk will be categorized according to HAS-BLED score; low risk (0-1), intermediate risk (2), and high risk ( $\geq 3$ ).
  - Bleeding risk assessment using the HEMORR2HAGES score which consists of the following variables: Hepatic/renal disease (1 point each); ethanol abuse (1 point); malignancy; age  $> 75$  y (1 point); low platelets count (1); re-bleeding risk (2 points); high blood pressure (1); anaemia (1); genetic factors (1 point); falls risk (1 point); stroke (1). All these variables will be identified using Read codes (Appendix 3 and 4), except for age, to build the score and assess patients’ risk for bleeding except for genetic factors which are not accurately captured in the CPRD.
  - Combined assessment of stroke, bleeding, and mortality risk using the GARFIELD-AF model relies on the following variables: age (in years), weight, heart rate, diastolic blood pressure, ethnicity, sex, history of bleeding, heart failure, history of stroke, diabetes, smoking status, dementia, use of antiplatelet, carotid occlusive disease, chronic kidney disease (CKD) (stages III–V) and vascular disease, in which the latter is defined as history of myocardial infarction (MI) or unstable angina, aortic or peripheral artery disease. These conditions will be identified using Read codes (Appendix 3 and 4).
- All risk assessment scores will be measured at each patient’s index date.

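### The predictor models combine age and sex with four risk scores that contain them, so their coefficients do not show the age and sex associations at equal comorbidity that aim 3 needs

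*Protocol*

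**What the plan says.** Protocol, Data/statistical analysis, item 1 (Phase 1): "To identify variables independently associated with OACs prescribing multivariate logistic regression models will be used and fitted with the covariates described in section N". Significance is set at P < 0.05. Item 3 (Phase 3) does the same for resumption of anticoagulants: "OACs after the indexed bleeding event multivariate logistic regression models will be used and fitted with the covariates described in section N". Plan for addressing confounding again points to the section N covariates for restarting treatment, there with a multinomial logistic model. By content, section N is Exposures, outcomes and covariates.

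The Phase 1 list in that section contains:
- "demographic information (age, gender, ethnicity, body mass index (BMI), geographic location (rural vs. urban), smoking status, alcohol consumption", with the Charlson index, frailty index, deprivation index and interacting drugs;
- CHA2DS2-VASc, whose items include "vascular disease, age 65 to 74 years, and sex category. Information included in the CHA2DS2-VASc score will be identified using Read codes";
- HAS-BLED, whose items include "history of bleeding or predisposition, labile INR, elderly";
- HEMORR2HAGES, with an item for age above 75;
- GARFIELD-AF: "Combined assessment of stroke, bleeding, and mortality risk using the GARFIELD-AF model relies on the following variables: age (in years), weight, heart rate", followed by further items that include sex, ethnicity and smoking.

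The Phase 3 list again holds age, gender and all four scores, measured at the index bleed. Nothing says that a score and its items will be kept in separate models.

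The Phase 1 models serve aim 3, which is to "assess the factors associated with not prescribing OACs including patient demographics, socioeconomic status, history of cancer and other comorbidities, stroke and bleeding risk".

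**The concern.** A coefficient in a multivariable model is read with every other term held fixed. When one of those terms is a score that already counts sex as a point, holding it fixed means that a woman must have one point less from something else than the man she is compared with. A patient aged 75 or over is likewise compared with a younger patient who has one or two more points from other items. These contrasts differ from the question whether age or sex is associated with prescribing among patients with the same conditions.

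Prescription of anticoagulants is the Phase 1 primary outcome, and predictors of under-prescription lead the stated objective and rationale. A reader of the results would take a significant sex coefficient as evidence that women are treated differently. It could instead be a by-product of how the score is built.

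**Working it through.** The protocol states no error rate or power for the predictor models, so there is no figure to reproduce.

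**1. Which items overlap (protocol definitions).**

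| Term | Age item | Sex item |
|---|---|---|
| CHA2DS2-VASc | yes | yes |
| HAS-BLED | yes | no |
| HEMORR2HAGES | yes | no |
| GARFIELD-AF | yes | yes |

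Alcohol is in HAS-BLED and HEMORR2HAGES and is also a covariate. Ethnicity and smoking are in GARFIELD-AF and are also covariates. Stroke recurs in all four scores, and bleeding history in three.

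**2. Algebra with one score.** Let C be the comorbidity points, A the age points and F the sex point, so S = C + A + F. Suppose log-odds of treatment = a + b·C, with no age or sex effect. Because C = S − A − F, the same model reads a + b·S − b·A − b·F. The sex coefficient is then −b although sex plays no part. With b = 0.25 (assumed) the odds ratio for women is exp(−0.25) = 0.78.

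**3. Simulation with all four scores.** From the protocol: at least 120,000 incident cases (counted in GOLD alone) and about 12% untreated. Assumed: mean age 75 (SD 11); 47% female; 16 comorbidities at 2–55%, most rising with age; GARFIELD-AF as a linear predictor. Assumed log-odds effects on treatment: stroke +0.5, hypertension +0.3, heart failure +0.2, diabetes +0.2, bleeding −0.6, anaemia −0.4, dementia −0.6, falls −0.4, alcohol −0.5. Charlson and frailty indices were not included. Tests are two-sided Wald tests at 0.05, with 200, 100 and 20 runs at n = 2,000, 14,000 and 120,000. Four fits gave convergence warnings.

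Rejection rates at the three sample sizes, in that order:

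| What drives prescribing | Model | Sex | Age |
|---|---|---|---|
| Conditions only | scores + age + sex | 44%, 100%, 100% | 6.5%, 11%, 85% |
| Conditions only | components + age + sex | 4%, 6%, 5% | 6%, 7%, 10% |
| The scores | scores + age + sex | 7%, 5%, 0% | 5.5%, 8%, 10% |
| The scores | components + age + sex | 27%, 96%, 100% | 12%, 47%, 100% |
| Nothing | scores + age + sex | 4.5%, 7%, 0% | 4%, 3%, 5% |

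In the first row the odds ratio for women is about 0.75 and for age about 1.05 per 10 years; both are truly 1.

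**4. Sensitivity at n = 120,000 (25 runs each), conditions only.** The 12% refers to patients given neither anticoagulant nor antiplatelet, whereas the protocol's untreated group includes lone antiplatelet users. A 40% untreated share was therefore tried too. Comorbidity effects were scaled by 0.25, 0.5 and 1, and sex was given weight 0 or 0.15 in the GARFIELD-AF term.
- Sex: rejection 92–100%, odds ratio 0.75 to 0.94.
- Age: rejection 0–96%, odds ratio 1.00 to 1.06 per 10 years.
- If only prior stroke matters: age rejects in 100% (0.91), sex in 40% (0.97).
- If only dementia matters: age rejects in 100% (1.08), sex in 32% (0.97).

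A simpler model with CHA2DS2-VASc as the only score (n = 10,000, 0.25 per comorbidity point) gave an age odds ratio of 0.88 per 10 years. The age artefact therefore has no fixed sign.

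**The case against.** The strongest objection is that the artefact depends on how prescribers behave. Study background says that guidelines tie anticoagulation to CHA2DS2-VASc, and the Phase 1 covariates define eligibility by it. If prescribing follows the scores, the planned model keeps error near nominal, and it is the component model that shows age and sex as significant. This stands as a limit on the claim. It does not remove the need for a component model: in that setting women and older patients with equal conditions really are treated differently, through the score, and aim 3 would want to know. The route must be stated when the result is reported.

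Comparing the sexes at equal guideline stroke risk is also a legitimate question. That stands too, provided the contrast is named as such.

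The text speaks of models in the plural, an analysis plan may settle the terms, and Study type calls Phase 1 hypothesis generating. These points lower the severity. Even so, the protocol names a covariate set, and the plain reading is that the whole set enters.

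A reader might infer three stronger things that the documents do not support:
- **That the model will always produce false age and sex effects, in particular under-treatment of the old.** This depends on what drives prescribing, and with all four scores the age artefact mostly pointed the other way. The background concern is with patients over 85, and CHA2DS2-VASc adds no age points beyond 75. In a check with banded age and that score alone, 85+ versus 75–84 rejected in 3.5% of runs.
- **That all four scores contain sex.** Only two do.
- **That the model cannot be fitted.** Exact collinearity needs the single CHA2DS2-VASc conditions and age bands entered beside the score, and the Phase 1 list does not enter most of them separately.

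**Conclusion.** The point holds in a limited form. By the protocol's own definitions, the age and sex coefficients in the Phase 1 and Phase 3 predictor models do not measure association with prescribing at equal comorbidity. This part needs no simulation.

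The size of the problem is conditional. If prescribing follows individual conditions, a false sex effect is near certain at the expected Phase 1 size for the broad sets of effects tried (odds ratio 0.75 to 0.94), and less likely (32–40%) when a single condition drives prescribing. The age artefact can be absent or can go in either direction. If prescribing follows the scores, or nothing matters, error stays near 5%. All magnitudes rest on assumed prevalences, effects and GARFIELD-AF weights. Phase 3 was not simulated, and the protocol gives no size for it.

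This should be corrected as a cheap improvement. It does not invalidate the study, and it does not touch the Cox models, where the scores serve only to adjust the anticoagulant effect.

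**What to change.** In Data/statistical analysis, items 1 and 3, and in the matching Phase 3 sentence under Plan for addressing confounding, replace the reference to the whole covariate list by two prespecified sets:

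- **A. Component model.** Age, sex, individual comorbidities, drugs, deprivation and ethnicity, with no composite scores. Statements about age, sex and comorbidities at equal comorbidity come from here. State that an age or sex association in this model may act through guideline scores. List the comorbidities by name.
- **B. One model per score.** The score plus only covariates that are not items of that score, for the association with stroke or bleeding risk. For example, the CHA2DS2-VASc model leaves out age and sex, while the HAS-BLED model leaves out age but may keep sex.

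Do not enter overlapping scores together in one predictor model. If the question is whether age or sex matters at equal guideline stroke risk, report that as a separate, labelled contrast. Say also where the Charlson and frailty indices belong, since they too summarise comorbidity.

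The cost is protocol wording and a few extra regressions. Most of the conditions are already to be coded in order to build the scores. The downside is that results come from several models instead of one.
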